### Intervention period

The intervention is designed to be implemented on hospital wards by clinical pharmacists who are already part of the patient care team. Each of the study wards in our study has a full-time equivalent clinical pharmacist present during weekday office hours, with a continuous presence established over the past 15 years before the study began. The pharmacists involved have varying levels of experience, from limited to more extensive, some of whom have a 1-year full-time postgraduate MSc in clinical pharmacy. All relevant details about the completed intervention components and any other actions taken by the pharmacist will be documented as usual in the patient’s EHR. The IMPACT-care intervention consists of the following four components (figure 2).

**Figure 2 F2:**

Overview of the IMPACT-care intervention, comprising four intervention components implemented during patient hospitalisation and post-discharge. *Based on the patient’s preference, this may include their informal caregiver. IMPACT-care, Improved Medication communication and Patient involvement At Care Transitions.

#### Component 1: Information package provided to patients and/or informal caregivers

In our pre-study,^22^ it was identified that medication-related discharge communication is not tailored to support patients’ self-care needs post-discharge. Additionally, patients were unprepared for medication-related consultations prior to discharge. To address these challenges, the research team, inspired by a similar intervention component developed in the UK,^36^ designed an information package consisting of a patient booklet (online supplemental material II) with input from clinical pharmacists at Uppsala university hospital and a panel of public representatives.

The booklet is designed to inform, prepare and engage patients and/or their informal caregiver in medication communication at discharge and self-care after returning home. It is organised into four sections: (1) hospitalisation course, (2) medications, (3) discharge and (4) advice on self-care. The first two sections feature a question prompt list,^37^ a set of discussion points intended to guide conversations with HCPs and encourage patients to actively participate in their care. The use of the questions prompt list has been found to enhance patient participation in medication-related communication.^38 39^ The third section contains a checklist of essential points for patients to review with HCPs to help confirm they have sufficient knowledge before leaving the hospital. The final section provides practical advice on seeking medication and general healthcare support after returning home.

Patients will receive the booklet in printed format at admission to the study ward and will be accompanied by an oral consultation with one of the researchers who also practices clinically as a pharmacist. During the consultation, the pharmacist will explain the content and guide the patient on how to use the booklet effectively. The booklet will also be available online. If the patient wishes, the pharmacist will provide the patient’s informal caregiver access to the information package. This can be done in person if the caregiver is present at the ward or remotely via phone, guiding them on how to access the materials online.

#### Component 2: Preparation of medication-related discharge documentation

Incompleteness and poor quality of medication-related discharge communication from hospitals is a common problem,^40 41^ making it difficult for subsequent HCPs to trust this information.^12 17 42^ Pharmacist involvement can significantly improve the completeness and quality of such communication.^40 41^ Consequently, in our study, the pharmacist will review relevant parts of the patient’s EHR and medication list prior to discharge to identify any lasting medication changes made during the hospitalisation. The pharmacist will collaborate with the discharging physician to reconcile follow-up plans for these changes. All medication changes, including reasons for the adjustments (when known), planned treatment duration, follow-up plans and the ward’s phone number for any post-discharge inquiries from the patient, will be documented in a standardised manner in the EHR by the pharmacist. This documentation will form the basis for detailing medication changes and follow-up plans in the patient’s discharge letter and the discharge summary intended for the next healthcare provider, both of which are written by a ward physician.

#### Component 3: Facilitation of discharge communication

To increase the likelihood that patients and their informal caregiver remember and use the booklet provided to them during intervention component 1, the pharmacist will consult the patient as the discharge date approaches. The consultation will include a review of the booklet’s content and a reminder to use it. If the patient wishes, the pharmacist will also contact the patient’s informal caregiver, either by phone or face-to-face, depending on the situation, to review the booklet and remind them to use it.

Informal caregivers are considered valuable support in helping patients recall information and manage self-care after returning home.^12^ However, they are often involved in a limited way in medication-related discharge communication by HCPs.^22 43^ To address this gap, the pharmacist in our study will arrange for an informal caregiver to attend the discharge consultation with the physician, if the patient so wishes. The pharmacist will contact the informal caregiver by phone once the discharge date is confirmed—no later than the morning of discharge—and invite them to participate in the consultation. Participation can be in person, by phone, or via video call depending on their availability. The pharmacist will then inform the discharging physician that the patient has requested their informal caregiver’s involvement in the discharge consultation.

#### Component 4: Follow-up call to patients or their informal caregiver

The timing of medication-related discharge communication often occurs at a suboptimal moment for patients, making it difficult for them to retain and recall the information after returning home.^22^ Incorporating intervention components both during hospitalisation and after discharge can help support medication continuity in older patients and bridge transitions.^44^ Telephone follow-ups, in particular, have shown promise in enhancing this support.^44^ Therefore, in our study, patients or their informal caregiver (based on the patient’s preference) will be offered a follow-up call with a clinical pharmacist post-discharge. If requested, the appointment for this call will be scheduled in consultation with the patient/informal caregiver, between 3 and 7 days after discharge, depending on the patient’s availability. The pharmacist will then contact the patient/informal caregiver at the agreed time. During the call, the pharmacist will start by addressing any questions the patient/informal caregiver may have, providing direct answers or referring inquiries to the appropriate HCP as needed. Following this, the pharmacist will review the medication-related discharge information, focusing on the updated medication list and details outlined in the discharge letter, including medication changes, reasons for the adjustments, planned treatment duration and follow-up plans. Additionally, the pharmacist will remind the patient of the advice on when and how to seek care, as presented in the booklet provided during intervention component 1.

### Outcomes

All outcomes will be assessed for participants from both the control and the intervention group (table 1).

**Table 1 T1:** Timeline and overview of the scheduled data collection for both the control and intervention group participants

	Admission	Discharge	Follow-up				
Time points (day)	−1*	0	7	14	30	90	120
Study inclusion							
Eligibility screening	x	x					
Informed consent	x						
Demographic data	x	x					
Outcome measures							
CMDD-M†		x					
PIMCH-Q‡			x				
Adherence to medication changes				x			x
Hospital revisits			x		x	x	
Hospital readmissions			x		x	x	
Emergency department visits			x		x	x	
Medication-related readmissions			x		x	x	

* Time point at which the patient is admitted to the study ward.

† CMDD-M, a point-based instrument using data from the patient’s electronic health records.

‡ PIMCH-Q, a questionnaire to patients measuring their perceptions of involvement in discharge medication communication and their confidence in post-discharge medication management.

CMDD-M, Complete Medication Documentation at Discharge Measure; PIMCH-Q, Patient Involvement in Medication Communication at Hospital Discharge Questionnaire.

#### Primary outcome

The improvement in the quality of medication-related discharge documentation will be the primary outcome, assessed using the average score from the Complete Medication Documentation at Discharge Measure (CMDD-M) (online supplemental material III).^45^ This point-based instrument, ranging from 0 to 9 points, is based on Swedish legislation^35^ outlining the requirements for written medication-related discharge documentation. The CMDD-M comprises five items, each scored from 0 to 1 or 0–2 points depending on the criteria. It evaluates the completeness and quality of medication-related discharge documents for individual hospital discharges, including the patient’s discharge letter, the discharge summary intended for the next healthcare provider and the presence of a follow-up request to bridge the gaps post-discharge. Improving the quality of discharge documentation is critical for ensuring continuity of care and patient safety during transitions of care.^17^ Poor-quality documentation has been associated with medication errors,^11^ non-adherence^46^ and avoidable need for medical care after discharge.^47 48^ By focusing the primary outcome on this domain, the trial aims to address an important gap in care that impacts patient outcomes.

#### Secondary outcomes

The proportion of patients with complete medication-related discharge documentation. This will be assessed using the CMDD-M to determine the prevalence of patients achieving the maximum score of 9 points.Improvement in patients’ perceptions of knowledge and involvement in discharge medication communication, and their sense of security in post-discharge medication management. This will be assessed by the average score by the Patient Involvement in Medication Communication at Hospital discharge Questionnaire (PIMCH-Q) (online supplemental material IV). It consists of eight statements rated on a 4-point Likert scale. It is designed with three dimensions: perception of knowledge, involvement and sense of security and aims to measure patients’ perceived involvement in medication communication during hospitalisation and their sense of security in managing medications after discharge. The questionnaire will be sent to patients 1-week post-discharge.Adherence to medication changes made during hospitalisation that persist post-discharge. This will be assessed by measuring the number of instances of non-adherence. Non-adherence to a medication change is defined as follows:New or modified medications: a medication initiated or modified during hospitalisation (ie, changes in strength, dose or formulation) that is not dispensed from a community pharmacy within 14 days post-discharge. This applies regardless of whether the reason is a missing prescription or the patient not filling the prescription. Changes in strength or dose are included only when they create a safety risk for the patient if the previous prescription is used (eg, reducing the dose of a tablet from 10 mg once daily to 2.5 mg once daily, which would require the patient to split the same tablet two times to get the correct dose, a practice considered unsafe).Discontinued medications: a medication discontinued during hospitalisation (or with altered strength or formulation), that is, erroneously dispensed using a previous prescription within 120 days post-discharge.The rationale for collecting data up to 120 days post-discharge is based on standard pharmacy practices in Sweden, where medications are typically dispensed for a 90-day (3-month) supply at a time. Patients may have leftover supplies of discontinued medications at home and continue using them. However, if these medications are not refilled at a pharmacy within 120 days, the patient is considered adherent to the discontinuation.The proportion of patients who are fully adherent to the medication changes made during hospitalisation that persist post-discharge. This will be assessed by determining the prevalence of patients who have no instances of non-adherence as described above.Unplanned healthcare visits post-discharge. This will be assessed using the following outcome measures:The prevalence of patients with at least one unplanned hospital revisit (a composite measure of unplanned readmissions and emergency department visits) at 7, 30 and 90 days post-discharge.The prevalence of patients with at least one unplanned readmission at 7, 30 and 90 days post-discharge.The prevalence of patients with at least one emergency department visit (not followed by admission) at 7, 30 and 90 days post-discharge.The time to the first unplanned hospital revisit within 90 days.The time to the first unplanned readmission within 90 days.The time to the first emergency department visit within 90 days.The prevalence of patients with at least one potentially medication-related hospital readmission at 7, 30 and 90 days post-discharge, assessed using the validated Assessment Tool to identify Hospital Admissions Related to Medications (AT-HARM10).^49 50^

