### Settings

The study is conducted in two surgical wards and one geriatric ward at Uppsala University Hospital in Sweden. The surgical wards mainly handle emergency surgeries, as well as liver-pancreas, transplantation, oesophagus-stomach, endocrine and colorectal surgeries. The geriatric ward treats older patients with complex acute medical and rehabilitation needs. These two clinical specialties were selected to assess whether the intervention could have an effect across various clinical settings.

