#### Adherence to medication changes

Data about the lasting medication changes made and prescribed during hospitalisation will be gathered from the EHR. Information on medications dispensed from pharmacies for each patient 120 days post-discharge will be obtained from the Swedish National Board of Health and Welfare’s national prescribed drug register. This register contains data on all medications dispensed from community pharmacies in Sweden on a patient level. The extracted data will include the medication name, the anatomical therapeutic chemical code, strength, prescribed quantity, collected quantity, prescription date, collection date, prescriber’s profession and workplace. The assessment of the number of instances of non-adherence will be conducted by the researchers.

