#### Secondary outcome analysis

Logistic regression will be used to analyse the prevalence of patients achieving the maximum score (9 points) on the CMDD-M, with results presented as ORs. The PIMCH-Q score will be analysed using linear regression models, evaluating the three dimensions both separately and in total. Differences in the number of instances of non-adherence to medication changes persisting post-discharge will be assessed using quasi-Poisson regression models, with results reported as rate ratios. Logistic regression models will be used to analyse the prevalence of patients who are fully adherent to medication changes persisting post-discharge, with results reported as OR.

The difference in the prevalence of patients with unplanned hospital revisits, unplanned readmissions, emergency department visits and medication-related readmissions at 7, 30 and 90 days post-discharge will be compared with logistic regression models, with results presented as ORs. Time to first unplanned hospital revisit, time to first unplanned readmission and time to first emergency department visit will be analysed using Cox proportional hazards models. Patients who do not experience the event by the end of the study period or are lost to follow-up will be censored at their last known follow-up time, while patients who die before experiencing the event will be censored at the time of death. Results will be reported as HRs.

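### The 14-day rule for new medicines has no exception for as-needed medicines, so a patient who follows an as-needed instruction can be scored as non-adherent in both adherence outcomes

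*Protocol article*

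**What the plan says.** The protocol article defines the outcome under Secondary outcomes: "This will be assessed by measuring the number of instances of non-adherence". For new or modified medicines the unit is "a medication initiated or modified during hospitalisation (ie, changes in strength, dose or formulation"). Such a medicine becomes an instance of non-adherence when it is one "that is not dispensed from a community pharmacy within 14 days post-discharge". The next sentence adds: "This applies regardless of whether the reason is a missing prescription or the patient not filling the prescription". One restriction follows: "Changes in strength or dose are included only when they create a safety risk for the patient if the previous prescription is used". Nothing is said about medicines to be taken only when needed.

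The companion rule for discontinued medicines is worded differently: it counts a dispensing only if it was made in error. A further secondary outcome, the proportion fully adherent, is the share of patients with no instance under the same definition.

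Under Adherence to medication changes, the lasting changes come from the health record and the dispensings from the national register: "This register contains data on all medications dispensed from community pharmacies in Sweden on a patient level". The register fields listed are name, ATC code, strength, quantities, dates and prescriber details. A dosing instruction is not among them.

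Under Secondary outcome analysis, "Differences in the number of instances of non-adherence to medication changes persisting post-discharge will be assessed using quasi-Poisson regression models", and full adherence is analysed by logistic regression. The exploratory interrupted time series also uses both adherence outcomes.

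**The concern.** For a medicine meant for regular use, failure to collect it within two weeks is a reasonable marker that the hospital's change was not carried through. For an as-needed medicine it is not. A patient who was prescribed it, had no need of it and left it at the pharmacy has done what was asked, yet the rule scores an instance.

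The binary outcome is the more sensitive of the two, because a single false instance moves the patient from fully adherent to not. The planned adjustment does not separate these instances: the covariates include ward type, number of lasting changes and number of discharge medicines, but nothing that distinguishes as-needed from regular use.

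The intervention may also act on collection itself. The pharmacist documents the reason and planned duration of each change and, for patients who ask for it, telephones 3 to 7 days after discharge, inside the 14-day window. That could raise or lower collection of unneeded as-needed medicines without any change in true adherence.

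**Working it through.** **Reading the rule.** Take a patient with one lasting change, a new as-needed medicine, prescribed at discharge, not needed and not collected by day 14.

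1. Was it initiated in hospital and does it persist after discharge? Yes.
2. Was it dispensed by a community pharmacy within 14 days? No.
3. Does the strength-or-dose restriction remove it? No, it is a new medicine.
4. Is there a test of whether collection was expected? No. The discontinuation rule has a test of error; this one has none.

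Result: one instance, not fully adherent.

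**Size.** The article states no adherence rate, as-needed share or power for these outcomes, so there is no figure of the plan's to reproduce. Only n = 115 per group and the two-sided 5% level come from the document (Sample size calculation; Statistical analysis). Every other input below is assumed.

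*How many patients.* If 20–60% leave with a new as-needed medicine and 20–40% of those do not collect it, the affected share is 0.20 × 0.20 = 4% to 0.60 × 0.40 = 24%. That is about 5 to 28 of 115 per group (4.6 to 27.6).

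*Fully adherent, equal false scoring.* Observed p = true p × (1 − q), where q is the share of truly adherent patients with at least one false instance. True p = 0.60 vs 0.75. Power is the normal approximation for two proportions.

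| q | Observed control | Observed intervention | OR | Power |
|---|---|---|---|---|
| 0 | 0.600 | 0.750 | 2.00 | 0.682 |
| 0.05 | 0.570 | 0.712 | 1.87 | 0.616 |
| 0.10 | 0.540 | 0.675 | 1.77 | 0.555 |
| 0.20 | 0.480 | 0.600 | 1.63 | 0.446 |
| 0.30 | 0.420 | 0.525 | 1.53 | 0.357 |

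*Count, equal false scoring.* Observed rate ratio = (λ₀ × RR + f) / (λ₀ + f), where λ₀ is true instances per control patient and f is false instances per patient. With RR = 0.70 and λ₀ = 0.5:

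- f = 0.10: 0.45 / 0.60 = 0.75
- f = 0.25: 0.60 / 0.75 = 0.80
- f = 0.50: 0.85 / 1.00 = 0.85

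With λ₀ = 1.0 the three values are 0.73, 0.76 and 0.80.

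*Fully adherent, unequal false scoring.*

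| q control | q intervention | True p (control, intervention) | Observed p | True OR | Observed OR |
|---|---|---|---|---|---|
| 0.10 | 0.20 | 0.60, 0.60 | 0.54, 0.48 | 1.00 | 0.79 |
| 0.20 | 0.10 | 0.60, 0.60 | 0.48, 0.54 | 1.00 | 1.27 |
| 0.10 | 0.20 | 0.60, 0.75 | 0.54, 0.60 | 2.00 | 1.28 |
| 0.20 | 0.10 | 0.60, 0.75 | 0.48, 0.675 | 2.00 | 2.25 |

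Equal false scoring pulls both effects towards 1. Unequal scoring can create an effect, hide one or enlarge one.

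**The case against.** The strongest reply is that this is a condensed article. It says that standard operating procedures for data collection exist, that researchers assess the instances, and that a full analysis plan will follow. Any of these may already handle as-needed medicines. That is possible, but the article does not leave the definition open: it gives a window, two reasons to be disregarded, a restriction and a worked example. A rule stated in that detail is fairly read as the rule. If an unshown procedure departs from it, the published definition should say so.

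Second, the sentence on reasons names only two, a missing prescription and an unfilled one. A reader might infer that non-dispensing counts whatever its cause. The text does not go that far. As-needed medicines come in because the definition has no exception for them, not because they are named.

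Third, the outcome deliberately counts missing prescriptions, which are not patient behaviour. It therefore measures in part whether the hospital's change reached dispensing. This stands, and it limits the remedy: excluding every as-needed medicine would also discard cases where the prescription was never issued.

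Fourth, the authors already say that precision was a worry and made adherence secondary for that reason. This bears on importance, but a general caveat does not correct a specific misclassification.

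**Conclusion.** The point holds for new as-needed medicines. As written, the rule can give a patient who follows the instruction an instance of non-adherence and remove that patient from the fully adherent group. It affects two secondary outcomes and their exploratory time-series versions. It does not touch the primary outcome, and the trial was not sized on adherence.

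Four stronger readings are tempting, and the document does not support them:

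- **That the adherence effects are diluted.** This requires false instances to be equally frequent in both periods. Otherwise the bias can go either way.
- **That medicines with a later planned start are wrongly scored in the same way.** Such a medicine is arguably not one initiated in hospital, so it is unclear whether the rule applies.
- **That clinic-administered medicines always score an instance.** The document does not say that they are assessed against pharmacy dispensing.
- **That the surgical wards guarantee many as-needed medicines.** Settings says "The surgical wards mainly handle emergency surgeries" and lists types of surgery. It says nothing about discharge prescribing.

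The size is unknown. The ORs, rate ratios and power above illustrate the mechanism on assumed inputs and are not estimates for this trial.

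**What to change.** Amend the definition for new or modified medicines, in the analysis plan and the data-collection procedure:

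1. When lasting changes are read from the health record, classify each new medicine as regular or as-needed from the order at discharge. Do this before dispensing data are linked, and identically in both periods.
2. In the main definition, do not count an as-needed medicine that was prescribed but not collected. Still count one for which the prescription is missing.
3. Where a counted medicine has a documented start after discharge, run the 14-day window from that start.
4. Confirm that only medicines meant for community-pharmacy supply are assessed.
5. Keep the present rule as a sensitivity analysis, so that the effect of the change is visible.

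The cost is one extra field in a record review that is already planned, and slightly fewer countable instances. Some patients who needed an as-needed medicine and did not collect it will no longer be counted; the sensitivity analysis retains them. The article says that the analysis plan will be finalised before any analysis, so the change can be made there. The discharge orders of control patients can still be classified from the health record.
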